#### Basic CCT (active control group)

This training application uses exercise tasks that are oriented towards parlour games and cognitive tasks for everyday life (see Table 3). The exercise tasks, like those of the individualised CCT, are playfully designed and require, among other things, simple strategies, basic arithmetic operations and long-term memory. This application involves five exercises that focus on the following key functions: visuoconstructional reasoning, working memory, semantic and autobiographical long-term memory and planning. Most of the exercises (e.g. the dice game) exist with only a single level of difficulty. The entry-level difficulties of the other exercises are determined solely by the participant’s prior successful results on this exercise. The exercises of the basic CCT aim to provide enjoyable computerised leisure activities with a limited number of cognitive tasks for the active control group.

### Measures

The data are being collected at baseline and follow-up by student assistants (psychology students) trained to conduct performance tests and interviews. The measures that are being used at the different measurement points are shown in Fig. 1.

**Fig. 1 Fig1:**
[figure not shown]
Timeline of measurements. Abbreviations. *CCT* computerised cognitive training, *MCI* mild cognitive impairment, *MoCA* Montreal Cognitive Assessment, *MMSE* Mini-Mental State Examination, *PHQ-9* Patient Health Questionnaire, *UEQ* User Experience Questionnaire. ^$^ The results of −t1 were used, since the timespan between the enrolment test and t0 is maximum 2 weeks

#### Primary outcome measure

##### Montreal Cognitive Assessment (MoCA) [26]

The MoCA is a performance test that is used to screen for MCI. It consists of more difficult items than the MMSE and is thus able to better detect MCI [26–29]. The score ranges from 0 to 30 points, with higher scores indicating better cognitive performance. A score ≤ 24 indicates cognitive impairment [24]. There are three parallel versions of the MoCA currently available. The MoCA has been found to be an appropriate measure for cognitive screening and has good values for validity and reliability [30].

#### Secondary outcome measures

##### Mini-Mental State Examination (MMSE) [31]

The MMSE is the most frequently employed screening test for dementia [32]. It measures five areas of cognitive functioning: orientation, registration, attention and calculation, recall, and language. The score ranges from 0 to 30 points, with higher scores representing better cognitive performance. Values above 23 points are interpreted as ‘not demented’, whereas scores between 0 and 23 indicate a dementia syndrome [25]. The reliability and validity of the MMSE has been established in numerous studies, e.g. [25, 33, 34].

##### Computerised cognitive assessment

Both versions of the computerised training application contain a set of exercises for measuring different cognitive abilities monthly, beginning at baseline. Eight tests are used to measure various cognitive abilities (see Table 4).

**Table 4 Tab4:** Computerised cognitive assessment

Test	Description	Adaptation of
Memory span I: Digit span, unsorted (‘Zahlen merken – unsortiert’)	Rows of single-digit numbers are presented (each 1 second); the numbers must be reproduced immediately afterwards	WAIS-IV [35], task Digit Span
Memory span II: Digit span, ascending (‘Zahlen merken – aufsteigend’)	Like Memory span I; numbers must be reproduced in ascending order	WAIS-IV [35], task Digit Span
Processing speed I: Number Comparison (‘Zahlen vergleichen’)	Comparison of two single-digit numbers separated by a horizontal line (participants should react if same number)	Pattern Comparison\Letter Comparison [36]
Processing speed II: Symbol count (‘Symbole zählen’)	Counting a target symbol in a pool as fast as possible	SKT [37], task ‘counting symbols’
Processing speed III: Numerical stroop task (‘numerischer Stroop-Test’)	Two single-digit numbers are presented in different sizes (congruent/incongruent mixed); number with higher value must be clicked as fast as possible	Numerical stroop task [38, 39]
Short term memory I: Free recall (‘Wortliste – Erinnern’)	12 objects have to be named; afterwards shown for 1 minute; some tests later, the objects must be remembered	SKT [37], task ‘delayed recall’
Short term memory II: Cued recall (‘Wortliste – erkennen’)	The objects from Short term memory I must be selected from a selection of 16 objects	SKT [37], task ‘recognition recall’
Logical reasoning: Matrices Test (‘Matrizentest’)	In a (2×2 or 3×3) matrix of symbols, the bottom right symbol is missing; the composition rule has to be understood, and the correct symbol must be selected	Raven Standard Progressive Matrices [40]

*Abbreviations*: *SKT* Syndrom-Kurz-Test (engl. Short Cognitive Perfomance Test), *WAIS-IV* Wechsler Adult Intelligence Scale – Fourth Edition

#### Other variables

##### The 9-Item Patient Health Questionnaire (PHQ-9) [41, 42]

The PHQ-9 is a short self-assessment tool often used in primary care settings to screen for depression [43]. Its nine items cover the nine DSM-IV criteria by asking patients about their experiences during the last 2 weeks and are rated on a four-point scale ranging from 0 (‘not at all’) to 3 (‘nearly every day’). The total sum score suggests varying levels of depression. A cut-off ≥ 12 was found to show a good balance between sensitivity and specificity [44]. The PHQ-9 was found to be a reliable and valid instrument for screening for depression [41].

##### Questionnaire on sociodemographic and health-related data

The following data are being recorded in a standardised questionnaire by the student assistants at baseline: sociodemographic data (age, sex, marital status, highest educational level, employment status, monthly income, household size), modifiable risk factors for MCI (status of general mental activities, physical activities, social participation, sleeping habits, average liquid intake, eating habits, alcohol consumption, nicotine consumption, visual/hearing capacity), non-cognitive symptoms (according to the symptoms of the Neuropsychiatric Inventory [45]) and health-related data (diseases, medications, body weight, body height, dementia cases in family history).

##### User Experience Questionnaire (UEQ) [46]

The UEQ measures attractiveness, perspicuity, efficiency, dependability, stimulation, and novelty of software with 26 bipolar items. The questionnaire consists of pairs of contrasting attributes (e.g. ‘understandable’ vs. ‘not understandable’) that can be rated on a 7-point Likert scale. The UEQ was found to show a satisfactory level of reliability and construct validity [46].

##### Application specialised questionnaire

An application specialised questionnaire is used to identify usability issues. For each exercise, subjective difficulty, specific usability issues, and attractiveness are rated on a 5-point Likert scale. The usefulness and efficiency of the task instructions have to be rated as well.

##### Additional digital data

Both CCTs track usage data. The usage data include the duration of use, difficulty, success, and other parameters for each training task run.

### Data collection

The data are being collected at baseline (t0) and at the end of the 6-month intervention period (t6). As the span between screening and t0 is approximately 2 weeks, we use the MoCA and MMSE of the screening as baseline values. For the exploratory study question, the data are being collected on a yearly basis after the baseline assessment with no specified end point (see Fig. 1). Due to the COVID-19 pandemic, we decided to eliminate the risk of infection related to study participation. The trial will be conducted entirely virtually. All data will be generated via videoconferencing, telephone, or the computerised cognitive assessment that is integrated into the CCTs. The participants were instructed in an invitation mail or letter to prepare an undisturbed environment for the videoconferences. However, participants lacking the hardware for a videoconference or those who are not willing to take part in an assessment by videoconference will be given the option to come into the clinical research centre for their screening visit or follow-up. Testing with the MoCA and MMSE will be conducted via videoconferencing with the student assistants. Videoconferencing assessments with the MoCA and MMSE have very high reliability scores compared with face-to-face testing. The intraclass correlation coefficients (ICC) for the MoCA and the MMSE have been demonstrated in several studies and go up to ICC = 0.99 for the MoCA [47] and up to ICC = 0.92 for the MMSE [48]. The questionnaire on sociodemographic and health-related data will be sent to the study participants to prepare them for the telephone interview. The data collected by the computerised cognitive assessment during the 6-month intervention period will be obtained from the study participants.

### Data quality management

The student assistants involved in the study have been thoroughly trained for their tasks by the study headquarters’ staff. When the study participants have questions concerning the computerised interventions, they can contact the study headquarters by email. The quality of the data is guaranteed by strict data monitoring at the study headquarters for the total study period. Plausibility checks and logical considerations about the relationships between associated variables will be performed. Regular backups will be carried out and saved on an external hard drive.

### Patient and public involvement

Study participants or the public are not involved in the development, design, or conducting of the study. The public has been informed about the recruitment process and the study. In order to recruit study participants from the general population, we provided extensive information about our study through local newspapers, a local magazine for older adults, members of a regional health insurance company, and a regional senior club for retired people. The local newspapers will provide information about the study participants’ experiences with the computerised intervention at the end of the 6-month intervention period.

### Data analysis

All relevant data, sociodemographic, health-related, primary, and secondary outcome variables will be reported descriptively. In order to be able to assess the quality of the randomisation, the baseline data from the intervention and control groups will be tested for statistically significant differences. For the multivariate analyses, we will impute missing values using the expectation maximum algorithm. The primary hypothesis will be tested by calculating multivariate analyses according to the general linear model. To ensure the robustness of the results, we will perform both analysis strategies ‘intention to treat’ and ‘per protocol’. ‘Intention to treat’ evaluations are carried out with all cases still alive at the end of the intervention or observation period. The significance level is defined as alpha = 0.05. The data analyses will be performed using the ‘IBM SPSS Statistics 24’ software. The members of the data monitoring committee are [name]. [name] and one of his statistics experts from the Institute of Medical Informatics, Biometry, and Epidemiology, Friedrich-Alexander Universität Erlangen-Nürnberg, [name].

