### Sample size and effect size estimation

A power analysis was computed with 100 study participants who were distributed to the two groups of the 2x2 factorial variance-analytic experimental design with one repeated measurement (factor 1: two CCTs; factor 2: two time points). With 50 study participants in each group, alpha = 0.05, beta = 0.20 (corresponding to a power of 80%), a correlation between repeated measures of 0.5 and a nonsphericity correction of 1, we will have the power to detect effects with an effect size of *f* ≥ 0.14 (comparable to Cohen’s *d* ≥ 0.28).

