### Randomisation

Our external biostatistics partner is creating computer-generated randomisation lists (Institute of Medical Informatics, Biometry, and Epidemiology, Friedrich-Alexander University Erlangen-Nürnberg, [name]). All individuals meeting the inclusion criteria are randomised into one of the two groups (individualised CCT or basic CCT). Randomisation is software based and stratified by sex. Couples are assigned to the same group.

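### Significance tests on baseline data cannot measure the quality of the randomisation; a descriptive table and fixed covariates should replace them

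*Protocol article*

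**What the plan says.** In the Data analysis section the purpose comes first, "In order to be able to assess the quality of the randomisation", followed by the method: "the baseline data from the intervention and control groups will be tested for statistically significant differences". The same section also plans descriptive reporting of the sociodemographic, health-related, primary and secondary variables. It gives one significance level, "The significance level is defined as alpha = 0.05", after the text on the primary hypothesis and the analysis sets. It does not say which baseline variables are tested, how multiplicity is handled, or what follows from a significant result.

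Under Randomisation, an external biostatistics partner supplies computer-generated lists, and "Randomisation is software based and stratified by sex". MoCA, the primary outcome, is therefore not balanced by design. The candidate baseline variables are spread over several sections. The largest group is in the questionnaire section, which begins "The following data are being recorded in a standardised questionnaire by the student assistants at baseline". MoCA, MMSE, PHQ-9 and the eight in-app tests come on top.

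**The concern.** The article names a method and a purpose, and the method cannot achieve the purpose. If the lists were followed, the null hypothesis of each baseline test is true by construction. A significant result is then a chance finding and does not point to faulty randomisation. A non-significant result does not clear the trial either, because the influence of an imbalance on the primary comparison depends on its size and on how strongly the variable predicts the outcome. Whether it crosses 0.05 with 50 per arm is a different question.

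The stakes lie in interpretation. Readers may be told that randomisation was or was not adequate on evidence that cannot say so, and attention is drawn away from the useful step, which is to settle in advance that the primary model adjusts for baseline MoCA.

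**Working it through.** **1. The plan's own figure.** The sample size section assumes 50 per arm, two time points, "a correlation between repeated measures of 0.5 and a nonsphericity correction of 1", and claims 80% power for "effects with an effect size of *f* ≥ 0.14". For the group-by-time interaction, the noncentrality is f² × N × m / (1 − ρ) = 0.14² × 100 × 2 / 0.5 = 7.84. With 1 and 98 degrees of freedom the power is 0.792, which agrees with 0.80. So the planned contrast is the difference in change. In SD units δ it satisfies δ² / (2 × 2(1 − ρ)/50) = 7.84, so δ = √(7.84 × 0.04) = 0.56.

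**2. Number of candidate baseline tests.**
- Sociodemographic, without the stratified sex: 6
- Modifiable risk factors, with vision and hearing counted as one: 9
- Non-cognitive symptoms, counted as one: 1
- Health-related: 5
- MoCA, MMSE and PHQ-9 from screening: 3
- In-app tests: 8

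Total: 6 + 9 + 1 + 5 + 3 + 8 = 32.

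**3. False signals under sound randomisation**, taking 0.05 two-sided per test. The article does not state sidedness and does not tie the level to these tests.
- Expected number: 32 × 0.05 = 1.6.
- At least one, independent tests: 1 − 0.95³² = 0.81.
- At least one, simulated with an assumed common correlation: 0.79 at 0.1, 0.68 at 0.3, 0.52 at 0.5.
- Without the eight in-app tests: 1 − 0.95²⁴ = 0.71.
- Fewer independent tests: 0.23 for 5, 0.40 for 10, 0.49 for 13, 0.51 for 14. For 20 tests correlated at 0.5 it is 0.42.

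**4. What a non-significant MoCA test leaves open.** With 50 per arm the standard error of a mean difference is √(2/50) = 0.20 SD. The critical difference is t(0.975; 98) × 0.20 = 1.984 × 0.20 = 0.397 SD. An observed difference of 0.3 SD gives t = 0.3/0.20 = 1.5 and p = 0.14. By the normal approximation, about 11% of sound randomisations give a MoCA difference between 0.28 SD and this threshold.

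**5. Effect of such an imbalance if the model does not adjust.** Given a baseline difference d₀, the expected unadjusted difference in change moves by −(1 − ρ) × d₀. With ρ = 0.5 and d₀ = 0.3 this is 0.5 × 0.3 = 0.15 SD, against the arm that started higher. Relative to the planned 0.56 SD it is 0.15/0.56 = 27%. Adjustment for baseline MoCA removes this conditional shift.

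**The case against.** The strongest reply is that the sentence does little harm. No decision rule is attached to it, and nothing in the article makes the covariates, the model or the interpretation of the primary result depend on these tests. Few readers would call a randomisation failed because one or two of 32 comparisons reached 0.05. This stands, and it limits the claim.

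Three stronger readings are tempting, and the article does not support them:

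- *A sound randomisation will probably be declared faulty.* This needs all listed variables to be tested and a single p < 0.05 to count as failure. The article states neither. With 13 or fewer independent tests the chance of any signal is below one half.
- *A MoCA imbalance would go unnoticed.* The descriptive reporting planned in the same section would show the arm means whatever the p-value.
- *The tests wrongly treat couples as independent.* Couples are assigned together, but the article names no test and gives no number of couples, so nothing can be built on this.

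The 0.15 SD shift comes from chance imbalance combined with not adjusting. The baseline tests do not cause it, and deleting them alone would not remove it. It is also conditional on the observed imbalance: over all sound randomisations the type I error stays nominal. Covariates may already be set in an analysis plan that is not shown, since the article says only that a general linear model is used.

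It can also be said that the null is true only if allocation was carried out as listed, and that baseline tests might expose gross departures. That is fair, but a p-value cannot separate such a departure from chance. Comparing the list with the download links issued would address it directly. Likewise, the in-app tests run inside the assigned software, so the list alone does not guarantee their null. A difference there could reflect the software, and leaving them out still gives 0.71.

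**Conclusion.** The point holds as an error in a stated analysis: baseline significance tests cannot assess the quality of a randomisation taken from computer-generated lists. If the 32 listed variables were each tested at 0.05, about 1.6 false signals would be expected, and at least one would occur with probability 0.81 under independence or roughly 0.5 to 0.8 at the assumed correlations. The count and the use of 0.05 per test are assumptions, since the article fixes neither. In the other direction, MoCA differences up to about 0.40 SD are non-significant with 50 per arm, and one of 0.3 SD would move an unadjusted change contrast by 0.15 SD at the protocol's correlation of 0.5. The primary test is not invalid on this account, and no route from the baseline tests to the primary result is stated. The change is worth making because the stated inference is wrong and the remedy is cheap.

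**What to change.** Delete the sentence on baseline significance tests. In its place, state that baseline characteristics will be summarised by arm without tests, and that the primary general linear model includes screening MoCA and sex as covariates whatever imbalance is observed. Fix this before the outcome data are analysed by arm.

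The cost is a change of wording in the Data analysis section and a fuller specification of the primary model. Both covariates are already collected, so no participants, visits or measurements are added. If the analysis plan already contains the adjustment, only the deletion remains. On the protocol's own correlation, adjusting for baseline also lowers the variance of the contrast from 2(1 − ρ) = 1 to 1 − ρ² = 0.75 in units of the outcome variance. Comparing the allocation list with the links actually issued is optional. It would be a small extra procedure, and a direct check of whether allocation was followed.

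### EM fill-in followed by an ordinary general linear model either understates the standard error or dilutes the effect, depending on whether arm is in the EM model; the size depends on a missing share that the protocol does not give

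*Protocol article*

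**What the plan says.** The Data analysis section of the protocol article fixes four things that bear on this point.

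- Missing data: "we will impute missing values using the expectation maximum algorithm", for the multivariate analyses.
- Primary test: "The primary hypothesis will be tested by calculating multivariate analyses according to the general linear model".
- Analysis set: intention-to-treat "evaluations are carried out with all cases still alive at the end of the intervention or observation period". A living participant with no 6-month MoCA therefore stays in the analysis with an imputed value.
- Error level: "The significance level is defined as alpha = 0.05".

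The section mentions no multiple imputation, pooling, added residual, variance correction or likelihood analysis of the observed data. It does not say which variables enter the EM model or whether treatment arm is one of them. Under Eligibility of participants the article lists reasons for dropping out, but no expected rate appears anywhere.

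**The concern.** EM used as a fill-in replaces each missing 6-month MoCA with a prediction. The general linear model then counts that prediction as a measured score. Baseline MoCA is the screening value (Data collection), so missing values fall almost entirely at month 6.

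The consequence depends on a choice that the article leaves open:

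- **Arm in the EM model.** The effect estimate is unbiased when data are missing at random. The filled-in values carry no residual scatter and still add to the sample size, so the reported standard error is too small and the test rejects too often.
- **Arm not in the EM model.** Participants with missing values in both arms are predicted from one common line, so they show no treatment difference and the estimate is pulled towards zero.

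Neither choice gives both an unbiased effect and a standard error that is right for it. What is at stake is the single primary test and its confidence interval.

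**Working it through.** **Inputs.** From Sample size and effect size estimation: "With 50 study participants in each group", "a correlation between repeated measures of 0.5 and a nonsphericity correction of 1", alpha 0.05, power 80%, two groups by two time points, detectable f ≥ 0.14. Assumed: a two-sided test, normal scores with SD 1, and the share m of missing 6-month values.

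**Step 1: the plan's own figure.** For the group × time interaction, λ = f²·N·m_t/(1−ρ), with m_t = 2 time points. This gives 0.14² × 100 × 2 / 0.5 = 7.84. On 1 and 98 degrees of freedom the power is 79.2%, and exactly 80% needs f = 0.1415. The stated figure reproduces. On the scale of change, the SD is √(2(1−0.5)) = 1 and the SE is √(2/50) = 0.20. The matching difference in change is 0.56 SD, since (0.56/0.20)² = 7.84.

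**Step 2: arm in the EM model.** With baseline as the only other predictor, EM for this pattern is the regression prediction from participants with observed 6-month scores. The t test on change is the group × time test. For ρ = 0.5, treating the slope as known:

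- Reported SE ≈ √[(1 − m + 0.25m) × 2/50]
- True SE ≈ √[2 × (0.75/(50(1−m)) + 0.25/50)]
- Type I error ≈ 2 × [1 − Φ(1.984 × reported/true)]

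| Missing | Reported SE | True SE | Ratio | Type I, formula | Type I, simulated |
|---|---|---|---|---|---|
| 3% | 0.198 | 0.202 | 0.98 | 5.2% | about 5% |
| 5% | 0.196 | 0.204 | 0.96 | 5.6% | 5.9% |
| 10% | 0.192 | 0.208 | 0.92 | 6.7% | 7.4% |
| 20% | 0.184 | 0.218 | 0.85 | 9.3% | 10.2% |
| 30% | 0.176 | 0.230 | 0.77 | 12.9% | 13.9% |

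The simulations (missing completely at random; 20,000 null trials per scenario from 5% up) run slightly higher because the slope is estimated.

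**Step 3: sensitivity of the arm-in result at 10%, 20% and 30% missing.**

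- Correlation 0.7: 7.6%, 10.7%, 15.0%.
- Missingness dependent on baseline (nominal rates, correlation 0.5): 8.3%, 11.1%, 15.4%.
- One random residual added to each filled-in value: 6.9%, 9.2%, 11.6%.
- One strong auxiliary in the EM model (6-month score plus noise of SD 0.6, assumed): 5.6%, 6.2%, 7.3% at correlation 0.5, and 5.7%, 7.6%, 8.4% at 0.7.

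**Step 4: arm not in the EM model.** Expected estimate = 0.56 × (1 − m), that is 0.504, 0.448 and 0.392 at 10%, 20% and 30% missing. Simulation agrees (about 0.51, 0.45, 0.39). Power falls from about 79% with complete data to about 75%, 66% and 59%. Type I error stays near 5%. Coverage of the true effect by the 95% interval is 94%, 90% and 83%.

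**Step 5: proper handling of the same data.** Null rejection at 10%, 20% and 30% missing was 5.2%, 4.0% and 4.8% with multiple imputation (20 datasets, arm included, Rubin's rules). It was 4.8%, 5.5% and 4.7% with a baseline-adjusted analysis of observed 6-month values. Both are close to nominal, so the defect comes from the fill-in and not from missing data as such.

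**The case against.** The strongest reply is that the article is a condensed account and says little about the EM step. That the fill-in is done once and analysed as observed is an inference, and the list of EM variables could sit in an analysis plan that is not shown. The trial also collects MMSE, eight monthly in-app tests and many baseline covariates. An EM model using them would predict the missing scores better than baseline MoCA alone, and with little missing data the problem is negligible.

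Much of this stands, and it limits the size of the point:

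- A reader might infer that type I error in this trial will be 7–15%. The document does not support that: the range corresponds to an assumed 10–30% missing and an EM model without auxiliaries.
- A reader might also infer that the standard error is wrong in every case. With arm left out it is right for the diluted estimate, and false positives are not increased. The harm there is bias towards zero, lost power and poor coverage of the true effect.

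What does not stand is that the matter is merely left to the analysis plan. The article names its method, and naming EM followed by a general linear model without pooling is a choice. Auxiliaries reduce the inflation but do not remove it, and participants who drop out may lack the late in-app tests that would help most. The per-protocol analysis is no safeguard: it addresses a selected population and does not correct the intention-to-treat standard error.

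**Conclusion.** The point holds conditionally. Read naturally, the stated method gives a standard error that is too small if arm is in the EM model, and a diluted effect if it is not.

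With arm in and only baseline MoCA besides, type I error is about 5–6% at 3–5% missing, 7–8% at 10%, 10% at 20% and 13–15% at 30%. With one strong auxiliary it is about 5.5–8.5% over 10–30% missing. With arm out, the effect shrinks by the missing fraction, and power falls to about 75%, 66% and 59% at 10%, 20% and 30% missing.

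These sizes rest on the protocol's 50 per group and correlation 0.5 (0.7 as sensitivity), on the group × time test being the primary test, and on assumed missing shares and auxiliary strength. With no missing 6-month scores there is no problem. The method is still worth replacing before analysis, because it governs the primary test and sound alternatives need no new data.

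**What to change.** For the primary test, replace the EM fill-in with one of these:

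1. A likelihood (REML) repeated-measures mixed model on all observed MoCA values, with arm, time and their interaction.
2. Multiple imputation that includes arm, baseline MoCA, sex, age, education and a small pre-specified summary of the in-app tests, pooled by Rubin's rules. All 8 tests at 7 occasions would be 56 variables for 100 participants, too many for a stable imputation model.

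Both are valid under missing at random with a correctly specified model.

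The cost is analysis wording and some syntax, with no new visits or participants. Compared with EM fill-in with arm included, confidence intervals become wider. Simulated ratios of reported to true SE of 0.92, 0.85 and 0.74 give 1/0.92 = 1.09, 1/0.85 = 1.18 and 1/0.74 = 1.35, so roughly 9%, 18% and 35% wider at 10%, 20% and 30% missing. The widening is smaller with good auxiliaries.
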